### Statistical approach

Statistical analysis will be performed by using SPSS 21.0 by third-party companies that have no access to the blinding codes, and we will not perform any subgroup analyses. If the primary outcome measure has superior efficacy in one group over the other, a confidence interval will be used for analysis. The secondary end point will be analyzed by a two-tailed test, and significance level will be α of 0.05 (otherwise stated). Continuous variables will be described by the mean and standard deviation. Categorical data will be described by the percentage, frequency, and composition ratio. All effectiveness and safety analyses will be strictly conducted in accordance with the intention-to-treat principle, the full analysis set (FAS) population, the per protocol set (PPS) population, and the safety set (SS) population. A *P* value of less than 0.05 will be considered statistically significant [10].

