### Outcomes

The primary outcome is LVEDVI = left ventricular end-diastolic volume/body surface area (LVEDV/BSA) and will be detected by three-dimensional ultrasound. The combined secondary outcomes include TCM syndrome score, echocardiogram results, 6-minute walk test results, Seattle Angina Questionnaire score, cardiac magnetic resonance imaging (CMRI) results, biological indicators (growth stimulation expressed gene 2 [ST2], galactose-specific lectin 3 [galectin-3], NT-proBNP, IL-1β, CRP, TNF-α, MMP-2, MMP-9, TIMP-1, TGF-β1, and CTGF), dynamic electrocardiogram results, and experiment event rate (hospitalization rates for HF, death rate of cardiovascular disease, or MI).

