**Efficacy evaluation**				
Echocardiogram	√	√		√
Cardiac magnetic resonance imaging		√		√
Biological indicator	√	√	√	√
Dynamic electrocardiogram	√	√	√	√
Traditional Chinese medicine syndrome score	√	√	√	√
6-minute walk test	√	√	√	√
Seattle Angina Questionnaire	√	√	√	√
Experiment event rate		√	√	√

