### Follow-up protocol

The follow-up for all participants will be scheduled at 4, 8, and 12 weeks. The primary and secondary outcomes as well as safety will be evaluated at each follow-up. AEs, especially severe AEs, are to be reported to the research group committee and ethics committee within 24 h. If the principal investigator determines that the AEs may be related to the experimental drugs, the blinding code will be opened and the testing of this subject will be terminated at the same time. All of this must be recorded on the case report form (CRF) and noted to the monitors.

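### Mean and SD, with an unadjusted two-sided 0.05, are a poor fit for eleven biomarkers measured at three post-baseline visits; log-scale, baseline-adjusted ratios labelled exploratory would serve better at no cost

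*Protocol article*

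**What the plan says.** All of this comes from the protocol article; no separate analysis plan is shown.

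- **Markers.** The Outcomes section lists among the secondary outcomes "biological indicators (growth stimulation expressed gene 2 [ST2], galactose-specific lectin 3 [galectin-3], NT-proBNP, IL-1β, CRP, TNF-α, MMP-2, MMP-9, TIMP-1, TGF-β1, and CTGF". That is eleven markers.
- **Timing.** Table 1, under Efficacy evaluation, ticks the row "Biological indicator" at V0, V1, V2 and V3. The Follow-up protocol section says: "The follow-up for all participants will be scheduled at 4, 8, and 12 weeks".
- **Decision rule.** The Statistical approach section says: "The secondary end point will be analyzed by a two-tailed test, and significance level will be α of 0.05 (otherwise stated". It adds that a P "value of less than 0.05 will be considered statistically significant". Nothing different is then stated for the biomarkers.
- **Summary rule.** The same section says: "Continuous variables will be described by the mean and standard deviation". No exception is made.
- **Role.** The study objective concerns LVEDVI alone. The Discussion calls ultrasound and cardiac MRI the major tools, and gives ST2 and galectin-3 as examples of markers that can also reflect fibrosis.

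**The concern.** Two general rules are applied to a family of variables that neither suits well.

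First, markers such as NT-proBNP, CRP and IL-1β cannot be negative and usually have a long right tail, probably longest at V0, soon after an infarct. A mean and SD then describe a patient who is not typical, and a few extreme values can drive the difference between arms. If the tests follow the same scale, a real proportional effect could be missed.

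Second, a flat 0.05 across up to 33 marker-by-visit comparisons makes an isolated significant marker weak evidence. The Discussion places the biomarkers beside imaging as evidence on remodelling, so a reader could give such a result more weight than it can bear.

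**Working it through.** The article gives no error rate or power for the biomarkers, so there is no figure of its own to reproduce.

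**Inputs from the article:** 11 markers (Outcomes); 3 post-baseline visits (Table 1); two-sided 0.05 (Statistical approach); 100 per arm (Sample size estimation, set there for LVEDVI and borrowed here).

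**Assumed inputs:** lognormal markers with log-scale SD *s* of 0.8, 1.0 or 1.2; a true 30% reduction; a correlation of 0.5 between log baseline and log follow-up; correlations between markers and between visits as shown. The article gives no marker distribution.

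**1. Mean and SD as a summary.** For a lognormal variable, SD/mean = √(exp(s²) − 1) and mean/median = exp(s²/2).

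| s | SD/mean | mean/median |
|---|---|---|
| 0.8 | 0.95 | 1.38 |
| 1.0 | 1.31 | 1.65 |
| 1.2 | 1.79 | 2.05 |

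The mean lies 38% to 105% above the median, and mean minus one SD is close to zero or negative.

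**2. Power, 100 per arm, ratio 0.70.** The log effect is ln 0.70 = −0.357. On logs, SE = s√(2/100) and power ≈ Φ(0.357/SE − 1.96). Adjustment for baseline multiplies SE by √(1 − 0.5²) = 0.866.

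- s = 0.8: SE 0.113; Φ(1.19) = 88%; adjusted Φ(1.68) = 95%.
- s = 1.0: SE 0.141; Φ(0.56) = 71%; adjusted Φ(0.95) = 83%.
- s = 1.2: SE 0.170; Φ(0.14) = 56%; adjusted Φ(0.47) = 68%.

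Simulation agrees to within about a percentage point and adds the raw-scale Welch test:

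| s | raw | log | log, baseline-adjusted |
|---|---|---|---|
| 0.8 | 77% | 88% | 95% |
| 1.0 | 52% | 70% | 82% |
| 1.2 | 33% | 56% | 68% |

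The step from raw to log is the cost of the scale. The step to the last column is a separate gain from using V0 values that are already collected.

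**3. At least one false positive, all markers null.**

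- 33 independent tests: 1 − 0.95³³ = 82%.
- 11 independent tests (week 12 only): 1 − 0.95¹¹ = 43%.
- Favourable direction only: 1 − 0.975³³ = 57%; 1 − 0.975¹¹ = 24%.

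With correlated test statistics (simulated multivariate normal, 11 × 3):

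| Between-marker | Between-visit | Either direction | Favourable only |
|---|---|---|---|
| 0 | 0.5 | 77% | 50–51% |
| 0.3 | 0.5 | 71% | 40% |
| 0.5 | 0.7 | 55% | 28–29% |
| 0.5 | 0.9 | 45% | 23% |
| 0.7 | 0.5 | 48% | 24% |
| 0.7 | 0.9 | 34% | 17% |

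So the either-direction figure is about 55–82% for between-marker correlation up to 0.5 and between-visit correlation up to 0.7. At between-marker correlation 0.7 it is 34–53%, and below one half once between-visit correlation reaches 0.5. At week 12 alone it runs from 43% (independent) to 30% (between-marker correlation 0.5).

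**The case against.** The strongest reply is that the article fixes less than it seems to.

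- **Thirty-three tests are not stated.** Evaluating outcomes at each visit is an assessment schedule. A repeated-measures model or a week-12 comparison would fit the text equally well. This stands, so the 33-test figures are conditional.
- **Mean and SD is a rule of description.** No raw-scale test is named and no transformation is ruled out. This stands too. The power loss follows only if raw values are tested, and its size rests on assumed log-scale SDs. What remains is the summary itself, which the article does prescribe for every continuous variable.
- **Multiplicity and transformation commonly sit in the analysis plan.** Their absence from an article is no error, and none is claimed. The point rests on the two rules that the article does state.

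A reader might go further and infer that an inert product would more likely than not yield a false anti-fibrotic finding. The documents do not support that. Such a finding must be in the favourable direction, which brings the risk over 33 tests to about 28–57% across the same correlation range, and above one half only near independence. Counting only seven fibrosis or matrix markers (an assumed grouping: ST2, galectin-3, MMP-2, MMP-9, TIMP-1, TGF-β1, CTGF), it is at most 1 − 0.975²¹ = 41%. Nor does the article say that one positive marker would establish an effect.

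A reader might also infer that the SD of these markers must equal or exceed the mean. For a lognormal variable that needs a log-scale SD of at least √(ln 2) = 0.83, and the article has no data on this.

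**Conclusion.** The point holds as a low-cost improvement in how the biomarkers are summarised, analysed and read; it is not an error that threatens the trial's main conclusion. The stated rules do cover all eleven markers, and mean and SD is a poor choice for those likely to be skewed. If testing follows the same scale, the loss is about 11, 18 and 23 percentage points of power at log-scale SDs of 0.8, 1.0 and 1.2, and baseline adjustment would recover a further 7 to 12 points. These sizes depend on the assumed lognormal shape, the 30% effect and the baseline correlation of 0.5.

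On false positives, even the mildest reading (one visit, correlation up to 0.5) leaves a risk of 30% or more of some significant marker in one direction or the other. That is enough to call for an exploratory label. The error rate of the LVEDVI analysis is not touched.

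**What to change.** In the Statistical approach section, or in the analysis plan before unblinding:

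1. Exempt the biomarkers from the mean-and-SD rule; report median and quartiles, or geometric means.
2. Analyse each marker on the log scale, adjusted for its log V0 value, and report the between-arm ratio with a 95% confidence interval.
3. Name week 12 as the main time point, and state that biomarker P values are unadjusted for multiplicity and exploratory.

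A formal hierarchy is optional, for example Holm on ST2 and galectin-3 with false-discovery-rate control for the rest. The Discussion offers those two only as examples, so ranking them is a choice for the trial team.

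The cost is wording only: no new samples, visits or patients. The one drawback is that isolated significant markers could no longer be presented as established effects.

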### Data management and monitoring

During the study, all eight organizations will be monitored bimonthly by the clinical research associate, which has no conflict of interest with the sponsors or researchers. All of the data from the eight organizations will be entered into the clinical data management system by two research assistants. Several measures, including the validation of values, referential data rules, range checks, and consistency checks against data already stored in the database, will be taken to ensure data integrity. Missing or incorrect data will be detected by software programs. All of the modifications of written documentation will be checked by electronic logs and audit trials. Original CRFs will be maintained for five years after the completion of the study. All of the authors will share their raw data and deposit it in the Electronic Data Capture repository (website: http://39.97.182.70:8082/tmyxw/).

## Discussion

Cardiac remodeling, which is the basic mechanism of the occurrence and development of HF, also determines the cardiac function and prognosis of AMI. Prevention and reverse cardiac remodeling play an important role in the treatment of MI.

Cardiac remodeling following MI occurs in both infarct and non-infarct areas, and the major processes include inflammation, cell death, myocardial stunning, hibernating myocardium, myocardial fibrosis of diffused foci or of the whole heart, and scar formation. Remodeling of the infarct area occurs mainly at the early stage of MI and eventually forms scars that are composed mainly of collagen. The remodeling of the non-infarct area usually occurs at the later stage of MI, and cell hypertrophy and fibroblast proliferation are the earliest pathological manifestations. Over time, abundant secretion and deposition of collagen, myocardial compensatory hypertrophy, myocardial interstitial fibrosis, myocardium stiffness, and the enlargement of the cardiac chamber result in progressive loss of ventricular function [11].

TMYX, an effective patent medicine that is commonly used to treat CHD, arrhythmias, and HF, has bright clinical application prospects. With regard to the different pathophysiological factors of cardiac remodeling, previous studies of TMYX have indicated that TMYX can inhibit cardiac hypertrophy; decrease the apoptosis rate of myocardial cells; decrease anti-inflammatory, antioxidant, antiarrhythmic, and myocardial protection; promote angiogenesis; and ameliorate cardiac energy metabolism in a rat model of MI and ischemic reperfusion injury [12–14]. Currently, cardiac ultrasound (CUS) [5, 15, 16] and CMRI [5, 17] are the major tools for the evaluation of ventricular remodeling and myocardial fibrosis at the international level. Above that, some biological indicators can also reflect the progress of fibrosis, such as ST2 and galectin-3 [5, 18–20]. In this trial, patients who have AMI and who receive PCI within 10 days will be the subjects, and the evaluation methods will include CUS; the T1 mapping sequence, cine sequence, and late gadolinium enhancement (LGE) sequence of CMRI; and measurements of biological indicators that reflect the progress of fibrosis. In other words, this trial is designed to demonstrate that the addition of TMYX to conventional treatment will intervene in the development of cardiac remodeling and cardiac dysfunction.

## Trial status

The kickoff meeting of the program was held in Zhengzhou, Henan Province, China, on April 21, 2019. The first participants were recruited in August 2019. All of the participants are scheduled to be enrolled by December 2020. The final amendments (version 2019-V-1.2) occurred on May 22, 2019.

## Abbreviations

CHD: Coronary heart disease
PCI: Percutaneous coronary intervention
AMI: Acute myocardial infarction
HF: Heart failure
CRF: Case record form
TMYX: Tongmai Yangxin pill
CUS: Cardiac ultrasound
CMRI: Cardiac magnetic resonance imaging
ST2: Growth stimulation expressed gene 2
Galectin-3: Galactose-specific lectin 3
MI: Myocardial infarction
LVEDVI: Left ventricular end-diastolic volume index
LVEDV: Left ventricular end-diastolic volume
TCM: Traditional Chinese medicine
ACEI/ARB: Angiotensin-converting enzyme inhibitor/angiotensin II receptor antagonist
AE: Adverse event
